### Plans for collection, laboratory evaluation, and storage of biological specimens for genetic or molecular analysis in this trial/future use {33}

Not applicable, as no biological specimens will be collected.

## Statistical methods

### Statistical methods for primary and secondary outcomes {20a}

Primary analysis will be performed following the intention-to-treat (ITT) principle, so each participant will be analyzed in the group he or she was randomized to. Absolute and relative frequencies will be determined for the primary endpoint (T2EL 12 months after index procedure) for both study groups. For patients that do not have a valid T2EL assessment at Visit 4 (12 months, including patients who died unrelated to the index procedure), the result of the 6-month evaluation will be imputed. A multiple imputation approach will be performed to impute missing values of participants with missing assessments at Visit 3 and Visit 4 (6 months and 12 months after index procedure, including patients who died unrelated to the index procedure before Visit 3). Age, sex, and study group will be considered in the imputation approach. Logistic regression models with the presence of T2EL at 12 months as dependent variable and study group, age, and sex as independent variables will be fitted to the imputed datasets. Results will be aggregated following Rubin’s rules, and an odds ratio with corresponding 95% confidence interval will be estimated and presented. Due to the small number of expected events, study centre will not be included as independent variable in the model. Sensitivity analyses based on complete cases only and on a per protocol set including only patients that were treated as described in the surgery SOP for their allocated study group will be conducted. Additionally, a time-to-event analysis considering death as competing event will be performed as sensitivity analysis.

Distributions of time to re-intervention, time to occurrence of endoleaks I/III, time to AAA rupture, and time to death will be estimated by Kaplan-Meier method or cumulative incidence function if competing risks are present. Logrank tests will be performed for group comparisons of (cause-specific) hazard rates. Categorical outcomes will be compared using Fisher’s exact tests or continuity-corrected chi-squared tests. For changes in quantitative outcomes (AAA diameter, quality of life), linear regression models with the corresponding change as dependent variable and study group and the baseline value as independent variables will be fitted to the data. All secondary endpoints will be analyzed in an exploratory manner. Effect measures (hazard ratios, odds ratios, mean differences) will be presented with corresponding 95% confidence intervals.

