### Participant timeline {13}

The frequency of study visits is equal to standard follow-up protocols after EVAR implantation (Table 1). CEUS will be used to determine the presence of an EL at 2–4 days, 30 days, 6 months, and 12 months after surgery. At 12 months, a CTA scan will be used as further imaging method. Patients additionally will be asked to answer a quality-of-life questionnaire after 12 months using a standard evaluation form (SF-36) [28].

**Table 1 Tab1:** Schedule of parameters and study visits. Visit timelines follow clinical routine

Visit	Screening/baseline	V0	V1a	V1b	V2	V3	V4
Months (m)/days (d)	−1–0 m		0–2 months (EVAR)	2–4 days after V1a	30 days	6 months	12 months
Eligibility criteria	+						
Informed consent ^a^		+					
Medical history ^b^, baseline characteristics ^c^		+					
Concomitant medication (esp. anticoagulation) ^d^		+	+^h^	+^h^	+^h^	+^h^	+
Randomization		+					
EVAR procedural details ^e^			+				
Details on AAA morphology ^f^/volume (CT-A), the presence of EL		+					+
The presence of EL, AAA diameter (CEUS)				+	+	+	+
Renal function ^g^		+		+			+
Adverse events			+	+	+	+	+
Reintervention				+	+	+	+
Quality of life (SF-36)		+					+

*CT-A* computer tomography with angiography, *CEUS* contrast-enhanced ultrasound. ^a ^The presence of a valid informed consent must be checked at the indicated study visits. ^b^ Medical history includes information on comorbidities (e.g. coronary heart disease, cerebrovascular disease, peripheral arterial disease, chronic obstructive pulmonary disease, malignancies, diabetes, arterial hypertension) and smoking habit. ^c^ Baseline characteristics include patient’s age and weight. ^d^ Medication includes information on antihypertensives, lipid-lowering agents, antiplatelet medication, and anticoagulation. ^e^ Procedural details include operation time and fluoroscopy time; in arm B, information on coils (e.g., type, length, number) and EVAR prosthesis (e.g. type, diameter). ^f^ Details on AAA morphology include length of neck, AAA diameter, number of efferent vessels (e.g. lumbar arteries, accessory renal arteries). ^g^ Renal function parameters include serum creatinine, serum urea, glomerular filtration rate. ^h^On these visits, only data on anticoagulation and antiplatelet medication will be captured

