### Sample size {14}

The primary aim is to reduce the proportion of T2EL in high-risk patients 12 months after the index procedure. The T2EL proportion in the control group after 1 year is assumed to be 45%. This assumption is based on a retrospective analysis of 100 consecutive patients treated at Klinikum rechts der Isar. The expected proportion of T2EL in the intervention group is 15%. This translates to an odds ratio of 0.22. The expected T2EL rates after 12 months in the respective groups are in accordance with the above mentioned RCT (41% vs. 14%; adjusted *OR* 0.19; 95% *CI* 0.05–0.71) [25].

Under these assumptions, 42 patients per group (84 overall) will be needed to detect a difference between the treatment groups with a statistical power of 80% (two-sided continuity-corrected chi-squared test, *α* = 5%). Due to potential loss to FU or incomplete FU, a total number of 50 patients per group is planned to be allocated to the study. Sample size calculation was performed using the software nQuery Advisor 7.0.

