### Methods in analysis to handle protocol non-adherence and any statistical method to handle missing data {20c}

For patients that do not have a valid T2EL assessment at Visit 4 (12 months, including patients who died unrelated to the index procedure), the result of the 6-month evaluation will be imputed. A multiple imputation approach will be performed to impute missing values of participants with missing assessments at Visit 3 and Visit 4 (6 months and 12 months after index procedure, including patients who died unrelated to the index procedure before Visit 3). Age, sex, and study group will be considered in the imputation approach.

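### Missing 12-month T2EL is filled with the 6-month result as a fixed value, or imputed from age, sex and study group, while the early CEUS results go unnamed

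*Protocol article*

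**What the plan says.** The rule stands in the Protocol article under Statistical methods for primary and secondary outcomes {20a} and is repeated under {20c}. It has two tiers.

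- **12-month assessment missing:** "the result of the 6-month evaluation will be imputed". The rule names deaths among the cases it covers, "including patients who died unrelated to the index procedure".
- **6- and 12-month assessments both missing:** multiple imputation. On its content the text says: "Age, sex, and study group will be considered in the imputation approach".

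The analysis model is a logistic regression of 12-month T2EL on study group, age and sex, pooled by Rubin's rules. The sensitivity analyses are complete cases, a per-protocol set, and a time-to-event analysis with death as a competing event.

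On the data available, Participant timeline {13} says: "CEUS will be used to determine the presence of an EL at 2–4 days, 30 days, 6 months, and 12 months after surgery". T2EL at the three earlier visits is also a secondary endpoint.

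**The concern.** Two features of the rule work against the primary estimate.

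First, a carried-forward value enters every imputed dataset as the same constant. Leaks that seal, are treated or appear between 6 and 12 months are misclassified, and Rubin's rules add no between-imputation variance for these patients.

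Second, the imputation for patients missing both visits uses the predictors of the analysis model. It therefore cannot correct for dropout that depends on early endoleak status. Such dependence is plausible because the trial is open-label and scan results are known. The early scans that could make a missing-at-random assumption credible are collected but not named.

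Missing data are a real prospect. The sample size allows for them, and the Discussion (Adherence to follow-up) notes that many patients in the earlier coil trial missed planned examinations for unknown reasons.

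The wording on deaths is also unclear: it mentions deaths unrelated to the index procedure and does not say how procedure-related deaths are handled.

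**Working it through.** **The plan's own figures** (Sample size {14}: 45% vs 15%, two-sided α = 5%, 80% power, continuity-corrected test)

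- Odds ratio: (0.15/0.85)/(0.45/0.55) = 0.216. The plan says: "This translates to an odds ratio of 0.22".
- Uncorrected n = [1.960·√(2·0.30·0.70) + 0.842·√(0.45·0.55 + 0.15·0.85)]²/0.30² = 35.4.
- Corrected n = (35.4/4)·[1 + √(1 + 4/(35.4·0.30))]² = 41.8, so 42 per group, as stated.
- Implied allowance for missing outcomes: 1 − 42/50 = 16%.

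**Step 1. Carry-forward, with missingness unrelated to T2EL.** Let p12 be the true 12-month proportion, r the share of 6-month leaks gone by 12 months, e the share of new leaks, and m the share missing only the 12-month visit. Then

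p6 = (p12 − e)/(1 − r − e), and the analysed proportion = (1 − m)·p12 + m·p6.

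The documents give no 6-to-12-month transition rates, so r and e are assumptions. With m = 16%:

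| r control / SE | e | Analysed control | Analysed SE | Difference (points) | OR |
|---|---|---|---|---|---|
| 0 / 0 | 0 | 45.0% | 15.0% | 30.0 | 0.216 |
| 10% / 10% | 2% | 45.6% | 15.0% | 30.7 | 0.210 |
| 20% / 20% | 3% | 46.5% | 15.1% | 31.4 | 0.204 |
| 30% / 30% | 5% | 47.6% | 15.1% | 32.6 | 0.195 |
| 40% / 10% | 2% | 49.7% | 15.0% | 34.7 | 0.178 |
| 10% / 40% | 2% | 45.6% | 16.2% | 29.4 | 0.230 |

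Example (row 3, control): p6 = 0.42/0.77 = 0.545, and 0.84·0.45 + 0.16·0.545 = 0.465. In all these rows simply dropping the missing patients would return 0.216, because missingness is unrelated to status. With m = 24% the OR range is 0.162–0.237.

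**Step 2. Precision.** Counting 50 rather than 42 patients per group as observed multiplies the standard error of the log OR by √(42/50) = 0.917, at fixed proportions. So if all 16% were carried forward, the standard error would be understated by at most about 8%, and by less the better the 6-month scan predicts the 12-month status.

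**Step 3. Both visits missing.** When only the outcome is missing and it is imputed from the analysis model's own covariates, the imputed values reproduce the fit to the other patients. The pooled estimate then equals the estimate without the imputed patients, apart from Monte Carlo noise.

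Assume 30-day T2EL of 58% (control) and 15% (SE), with 15% of leaks resolving and 3% new leaks per interval.

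- P(12-month leak | 30-day leak) = 0.85² + 0.15·0.03 = 0.727.
- P(12-month leak | no 30-day leak) = 0.03·0.85 + 0.97·0.03 = 0.0546.
- Truth: control 0.58·0.727 + 0.42·0.0546 = 44.5%; SE 0.15·0.727 + 0.85·0.0546 = 15.5%; OR 0.23.

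Now let dropout depend on the 30-day result in one arm, with 5% of 30-day-negatives missing there and 10% missing regardless of status in the other arm.

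- Control arm, 30% of positives missing: (0.58·0.70·0.727 + 0.42·0.95·0.0546)/(0.406 + 0.399) = 39.4%, OR 0.28. With 25% missing: 40.5%, OR 0.27.
- SE arm, 30% of positives missing: (0.15·0.70·0.727 + 0.85·0.95·0.0546)/(0.105 + 0.8075) = 13.2%, OR 0.19. With 25% missing: 13.7%, OR 0.20.

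Imputing from the 30-day result restores 44.5% and 15.5%, because missingness depends only on that result.

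Carry-forward alone in the same chain: the 6-month control rate is 0.58·0.85 + 0.42·0.03 = 50.6%. If 30% of those positives miss the 12-month visit, the analysed rate is 44.5% + 0.30·50.6%·0.15 = 46.7%, and the OR is 0.21.

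**Step 4. Both tiers together.** A large-sample simulation used 45% vs 15% at 12 months, about 10–21% missing per arm, 10–30% of leaks resolving and 3–5% new leaks per interval. The planned rule gave ORs of 0.199–0.214, with arm proportions shifted by up to about 1.6 points. Imputation from the 30-day and 6-month scans gave 0.212–0.218.

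**The case against.** Several points on the other side stand.

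- **Size.** At 50 per group, the standard error of the log OR is √(1/22.5 + 1/27.5 + 1/7.5 + 1/42.5) = 0.488, so an OR of 0.216 has a 95% interval of about 0.08–0.56. Every shift above is small beside that. The 25–30% dropout among leak-positive patients is an invented and severe input against a planned allowance of 16%.
- **Evidence.** The trials described under Previous trials give T2EL rates at 3 and 24 months, and at 12 and 24 months. Neither covers 6 to 12 months, and the first trial's convergence is attributed to reinterventions. Instability in the relevant interval is possible, not shown. The remark in the Discussion that few leaks occur or seal later concerns the time after 12 months, so it does not settle the question either way.
- **Complete cases.** A reader might infer that this sensitivity analysis merely repeats the primary one. It does so only for patients missing both visits. It also drops the carried-forward patients, so it is a partial check on that step.
- **Modality.** A reader might object that the 6-month scan is CEUS only. The endpoint accepts CEUS and/or CTA, and the Discussion describes CEUS as equally sensitive, so little rests on this.
- **Imputation variables.** The text does not say that only age, sex and group enter, and an unseen analysis plan could add more. Where a 6-month scan exists, the rule does use an earlier scan.

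What remains is that the carry-forward is an explicit rule of the primary analysis, stated twice. The named imputation set brings in no information beyond the analysis model, and no planned sensitivity analysis replaces carry-forward with model-based imputation.

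**Conclusion.** The point holds as a should-fix in a trial that calls itself exploratory. The rule can introduce bias where dropping the missing patients would not, overstates precision somewhat, and leaves collected information on 12-month status unused.

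Under assumed transition rates, carry-forward gives an OR of about 0.18–0.23 against 0.216 at 16% missing. Under assumed strong dependence of dropout on early T2EL in one arm, the imputation tier gives about 0.19–0.28 against 0.23.

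Two stronger readings are not supported. One is that the rule favours SE: equal resolution in both arms does push that way, but other scenarios push the opposite way, and the bias is zero if status is stable and missingness is unrelated to T2EL. The other is that procedure-related deaths fall out of the ITT set: the text never says so. The general rule covers any patient without a valid 12-month assessment, and with EVAR mortality put at about 1% in the Background, roughly one patient in 100 is concerned. That is a wording gap to close.

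**What to change.** In the primary analysis, multiply impute every missing 12-month T2EL status with one parsimonious model pooled over arms. It should contain study group, age, sex, the earlier CEUS T2EL results and, if numbers allow, T2EL re-intervention. Specify penalisation or another guard against separation. Keep the 6-month carry-forward and complete cases as sensitivity analyses. State how procedure-related deaths before Visit 4 enter the ITT analysis.

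The model must stay small. With 42 observed per group, about 0.45·42 + 0.15·42 = 25 events are expected in total, but only about 6 in the SE arm. A separate model per arm with about eight predictors is not workable: in a simulation with assumed covariates, ordinary logistic imputation of that size met separation in about 99% of SE-arm and 97% of control-arm datasets. Pooling assumes that earlier scans predict 12-month status similarly in both arms. Including re-intervention eases that assumption.

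The cost is a change of wording, slightly more analysis work and care with a small-sample imputation model. No new data or patients are needed, and the planned 42 evaluable and 50 allocated per group do not change.

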### Interim analyses {21b}

No interim analysis will be performed, unless demanded by the safety monitoring board (SMB).

### Methods for additional analyses {20b}

A subgroup analysis comparing treatment effects of the early study phase (patients recruited in the first year) with the late study phase (second year) will be performed. A logistic regression model including study group, study phase, and their interaction term will be fitted to the data to test for treatment effect heterogeneity in order to assess the presence of a learning effect. In an additional subgroup analysis, results will be shown stratified for study centre using the same approach as described for study phase.

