**Fig. 2 Fig2:**
[figure not shown]
Examples of intraoperative angiograms after endovascular aortic repair with sac embolization. Within the EVAR-SE study, a minimum of 2 m of coil material is to be implanted in the abdominal aortic aneurysm sac. It is aimed for homogeneous filling of the aneurysm sac with coils forming a lose network to trigger thrombus formation

Involved investigators have received a training course for the SE procedure and are asked to follow a clear standard operating procedure (SOP). In doing so, the choice of stent graft and coils will be left to the discretion of the operating surgeon. The procedure is simply applicable and easy to adopt for certified vascular surgeons; thus, the expected learning curve is expected to be negligible but will be statistically evaluated.

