## Current trial status

The latest protocol version (number 1.1; 24.11.2022) was approved by the domestic Ethics Committee of the Technical University of Munich in December 2022 and all other ethics committees of the respective study sites (respective reference numbers see below).

Initiation was completed at Klinikum rechts der Isar of the Technical University of Munich in December 2022, at St. Joseph’s Hospital Wiesbaden in June 2023, at the University Hospital Dresden in August 2023, and at the University Hospital Augsburg in September 2023.

The first patient was recruited on 13th January 2023. Until today (1st October 2023), a total of 19 patients have been randomized. Recruitment is estimated to be complete in the 1st quarter of 2025.

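### The learning-effect analysis splits patients by trial-wide recruitment year, which partly mixes centre with experience because three of the four centres opened 6 to 9 months after the first

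*Protocol article*

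**What the plan says.** Intervention description {11a}, in the text below the Fig. 2 legend, states that "the expected learning curve is expected to be negligible but will be statistically evaluated". Methods for additional analyses {20b} sets out how: a subgroup analysis "comparing treatment effects of the early study phase (patients recruited in the first year) with the late study phase (second year". On the model it says: "A logistic regression model including study group, study phase, and their interaction term will be fitted to the data", and the stated purpose is "to test for treatment effect heterogeneity in order to assess the presence of a learning effect". Centre is handled separately: "In an additional subgroup analysis, results will be shown stratified for study centre using the same approach as described for study phase". In the primary model (Statistical methods {20a}), "study centre will not be included as independent variable in the model", because few events are expected.

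Current trial status gives the opening dates. "Initiation was completed at Klinikum rechts der Isar of the Technical University of Munich in December 2022"; Wiesbaden followed in June 2023; then came initiation "at the University Hospital Dresden in August 2023, and at the University Hospital Augsburg in September 2023". The first patient was recruited on 13 January 2023, 19 had been randomised by 1 October 2023, and recruitment is expected to end in the first quarter of 2025.

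**The concern.** Learning belongs to an operator or a centre, but the protocol measures it on one calendar for the whole trial. If every centre had started together, recruitment year would be a rough but usable stand-in for experience. They did not. A patient treated early in year 2 may be among a late-opening centre's first SE cases, while a patient treated late in year 1 at the first centre may follow many SE cases there.

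Two things follow. Misclassified experience pulls a true learning effect towards zero. And because the centre mix differs between the two years, a difference between centres in the effect of SE can appear as a group-by-phase interaction. This is the only learning analysis that the article describes, so the reading of the learning curve rests on it.

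**Working it through.** **The plan's own figure.** The learning analysis has none. The trial's sample size does reproduce. For 45% vs 15%, two-sided 5%, 80% power: [1.96·√(2·0.30·0.70) + 0.842·√(0.45·0.55 + 0.15·0.85)]² / 0.30² = 35.4. With continuity correction, (35.4/4)·[1 + √(1 + 4/(35.4·0.30))]² = 41.8, so 42 per group, as stated.

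**Inputs.** The dates are those in Current trial status. Year 1 is taken as 13 January 2023 to 12 January 2024 (assumption: counted from the first patient). Only the month of initiation is given, so each later centre is placed first at the start and then at the end of its month. Per-centre recruitment is not reported, so relative rates are assumed.

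**Open months in year 1.** First centre 12; the others 6.5–7.4, 4.4–5.4 and 3.4–4.4. In year 2 all four have 12. Only one centre was certainly open from 13 January to 1 June 2023, which is 4.6 months.

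**Centre mix.** Share = (rate × open months) / sum over centres. Equal rates, start of month: 12/(12 + 7.4 + 5.4 + 4.4) = 41% in year 1, against 25% in year 2. Overlap is the sum over centres of the smaller of the two yearly shares.

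| Assumed rates | First centre, year 1 | Year 2 | Fall (points) | Overlap of centre mix |
|---|---|---|---|---|
| Equal | 41–46% | 25% | 16–21 | 79–84% |
| First centre 2× | 58–63% | 40% | 18–23 | 77–82% |
| First centre 3× | 68–71% | 50% | 18–21 | 79–82% |
| Each other centre 2× | 26–29% | 14% | 12–15 | 82–85% |

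**Leak of a centre difference, with no learning at all.** Assume a 45% control rate everywhere and a type II endoleak rate after SE of 15% at the first centre and 20–35% elsewhere. Example (first centre 2×, 35% elsewhere): year 1 SE rate = 0.61·0.15 + 0.39·0.35 = 22.8%; year 2 = 0.40·0.15 + 0.60·0.35 = 27.0%. The ratio of odds ratios is (0.270/0.730)/(0.228/0.772) = 1.25. Across the equal, 2× and 3× first-centre scenarios it is 1.06–1.25, against true between-centre ratios of 1.42–3.05. The leak is real but diluted. In this direction it works against an apparent learning benefit; if the later centres did better, it would imitate one.

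**Misclassified experience.** Take 50 SE cases over 24 months and later centres starting at months 5.1, 7.1 and 8.1. Expected year-1 SE cases per centre = rate × (12 − start). At equal rates the rate is 50/(24 + 18.9 + 16.9 + 15.9) = 0.66 per month, giving 7.9, 4.6, 3.2 and 2.6. With the first centre at 3×, they are 14.6, 2.8, 2.0 and 1.6. In a simulation of case order, with "early" meaning a centre's first 3 to 5 SE cases (assumption), 14–41% of those early cases fall in year 2, and 20–58% of year-1 SE cases are already past that point.

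**Size of the early group and power.** 19 patients in 8.6 months is 2.2 per month; the remaining 81 by 1 January 2025 would need 81/15 = 5.4 per month. Over the 3.4 months to 13 January 2024, year 1 reaches 19 + 2.2·3.4 ≈ 27 to 19 + 5.4·3.4 ≈ 37 patients, so 13–19 SE patients and, at 15%, 2–3 endoleaks. With 37 vs 63 patients and no losses, the variance of the interaction is Σ 1/[n·p(1−p)] over the four cells. For an SE rate falling from 25% to 10%, log ratio 1.10, SE 0.99, power 20%. For 35% to 8%, log ratio 1.82, SE 1.01, power 44%.

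**Unassigned patients.** If recruitment ran to 31 March 2025, the rate needed is 81/18 = 4.5 per month. The 2.56 months from 13 January would then hold 4.5·2.56 = 11.5, so 11 or 12 patients in neither phase. If it ended by 12 January, none.

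**The case against.** A reader might infer that the analysis compares centres instead of experience. The documents do not support that. All four centres were initiated before year 1 ended, all can recruit in both phases, and the centre mix overlaps by 77–85% under the rates tried. Nor do they support calling year 1 largely one experienced centre: no per-centre recruitment is given, equal rates put the first centre at 41–46%, and the article says that the investigators involved were trained and follow a standard procedure. Its remarks on its authors' own SE experience name no centre. It would also be too much to say that the later centres' first SE cases fall mostly in year 2: 1.6–4.6 SE cases are expected in each of them in year 1, so their very first cases mostly fall there. The gaps of 6 to 9 months are measured from the first centre; the other three opened within 3 months of one another.

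There are also safeguards. Randomisation is stratified by centre, so the treatment comparison within each phase is fair. The trial is declared exploratory. That a null result would be cited as proof of no learning is speculation, since the article states an expectation and a plan to evaluate it.

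All of this stands, and it limits the size of the problem. One defence does not stand: the separate centre analysis replaces phase with centre in the same kind of model, so no model holds both and neither result can be adjusted for the other.

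**Conclusion.** The point holds in limited form. Recruitment year is a weak and partly centre-dependent measure of experience here, and the model has nothing to separate the two. That follows from the stated dates and model alone. The sizes (a shift of 12–23 points in centre mix, 14–41% of early SE cases labelled late, a spurious ratio of odds ratios of 1.06–1.25) rest on assumed per-centre rates, an assumed cut at 3 to 5 cases and assumed centre differences. What is affected is the attribution of an interaction, or of its absence, to learning. With 20–44% power even for large assumed effects, a null result would say little about whether the learning curve is negligible. The gap after 12 January 2025 is minor and may turn out empty.

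**What to change.** Define experience as the number of in-trial SE procedures already done at that centre before the patient's EVAR date. This is defined in both arms and assigns every patient, so the gap after month 24 disappears. Use it in place of calendar year in the interaction with study group, either as log(count + 1) or as first k vs later, with the form fixed before analysis. Include centre as a main effect or stratum. Report the interaction descriptively with its confidence interval, and state that a null result is not evidence of a negligible learning curve.

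The cost is a change of wording in {20b} or the analysis plan. Centre is a randomisation stratum, and Table 1 already lists the EVAR visit with coil details for the SE arm.

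The limits should be stated too:
- About 50 SE patients at 15% give 7 or 8 endoleaks, so precision will be low.
- A centre main effect removes differences in the overall endoleak rate but not in the SE effect itself. Removing those needs group-by-centre terms (three more parameters with four centres), which so few events can hardly carry. The centre-stratified results should therefore be shown beside the experience result.
- Operator identity and SE cases done before or outside the trial are not listed as collected, so the count measures in-trial centre experience only.

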## Methods: participants, interventions, and outcomes

### Study setting {9}

The study is conducted at four dedicated vascular surgery centres in Germany. Besides, the Klinikum rechts der Isar of the Technical University of Munich, the University Hospitals of Augsburg and Dresden, and St. Josef’s Hospital Wiesbaden participate as recruiting sites. The study is conducted in conjunction with the Münchner Studienzentrum (MSZ; Clinical Trials Center at School of Medicine, Technical University of Munich).

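### The group-by-centre logistic interaction is likely to meet empty cells: about half of trials would have a centre odds ratio of 0 or infinity and an unreliable heterogeneity test

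*Protocol article*

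**What the plan says.** Under Methods for additional analyses {20b}, the article describes a subgroup analysis by early and late study phase: "A logistic regression model including study group, study phase, and their interaction term will be fitted to the data", in order to test whether the treatment effect differs. For centre, "results will be shown stratified for study centre using the same approach as described for study phase". The section names neither the type of interaction test (Wald, likelihood ratio or exact) nor a method for sparse cells.

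Study setting {9} fixes the number of levels: "The study is conducted at four dedicated vascular surgery centres in Germany". Sample size {14} gives the rates and numbers: "The T2EL proportion in the control group after 1 year is assumed to be 45"%, "The expected proportion of T2EL in the intervention group is 15"%, and 50 patients allocated per arm, of whom 42 are needed with an outcome. Statistical methods {20a} leaves centre out of the primary logistic model and gives the small number of expected events as the reason. It also says that effect measures, odds ratios among them, come with 95% confidence intervals.

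**The concern.** The primary model avoids three centre terms because events are few. The subgroup analysis then fits those three terms plus three interaction terms to the same events. A method that works for two phases is carried over to four centres without allowing for how thin the cells become.

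Ordinary maximum likelihood needs at least one event and one non-event in every arm-by-centre cell. Where a centre has no type II endoleak (T2EL) in its SE arm, its estimated odds ratio is 0, the log odds ratio has no finite value and no finite Wald interval exists. At stake is the planned check that the effect is consistent across centres, in a trial presented as multicentre and as testing an easily adopted technique. Its result could depend on the software's default test as much as on the data.

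**Working it through.** **Inputs.** T2EL 45% (control) and 15% (SE), 50 allocated and 42 evaluable per arm (Sample size {14}); four centres (Study setting {9}); roughly equal arms within centre, since randomization is blocked and stratified by centre (Sequence generation {16a}). Patients per centre are not stated, so splits are assumptions. Equal centres are the base case. Unequal ones are plausible because the centres were initiated between December 2022 and September 2023 (Current trial status).

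**Plan's own figure.** The article states "42 patients per group (84 overall) will be needed to detect a difference between the treatment groups with a statistical power of 80"%, by a "two-sided continuity-corrected chi-squared test" at 5%. The usual formula gives 35.4, so 36 per arm without correction. With the correction, 35.43/4 × [1 + √(1 + 4/(35.43 × 0.30))]² = 41.8, so 42 per arm. The odds ratio is (0.15/0.85)/(0.45/0.55) = 0.216, stated as 0.22. Both are reproduced.

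**Events per centre.** In the SE arm 0.15 × 50 = 7.5 or 0.15 × 42 = 6.3 events are expected. Over four centres that is 1.9 or 1.6 each.

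**Chance of a degenerate cell.** P = 1 − product over all eight cells of [1 − (1 − p)^n − p^n].

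- For n = 13 and n = 12 in the SE arm, the chance of no events is 0.85^13 = 0.121 and 0.85^12 = 0.142. Zero SE events in at least one of the centres 13/13/12/12: 1 − (0.879)² × (0.858)² = 0.431. Adding all other cells gives 0.433, so nearly all of the risk is zero events in the SE arm.
- For n = 11 and n = 10 (42 per arm), 0.85^11 = 0.167 and 0.85^10 = 0.197. The total is 0.557.

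| Per arm | Split over centres | SE rate 15% | SE rate 20% |
|---|---|---|---|
| 50 | 13/13/12/12 | 43% | 23% |
| 50 | 20/12/10/8 (assumed) | 52% | 33% |
| 50 | 25/10/8/7 (assumed) | 62% | 43% |
| 42 | 11/11/10/10 | 56% | 34% |
| 42 | 17/10/8/7 (assumed) | 64% | 44% |
| 42 | 21/8/7/6 (assumed) | 72% | 55% |

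**Phase model, for contrast.** With equal halves the risk is 3% (25/25) to 6% (21/21). Nineteen patients were randomized in the 261 days from 13 January to 1 October 2023; at that pace the first year gives 19 × 365/261 ≈ 26, or 13 per arm. A 13/37 split gives about 12%.

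**Behaviour of the 3-df test.** Trials were simulated (4,000 per scenario) with the saturated group-by-centre model and a nominal 5% level.

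- No heterogeneity: Wald rejects in 0.2% to 0.6%, ordinary likelihood ratio in 8% to 9% (11% to 17% among trials with a degenerate cell). Further simulation runs widen these ranges only to below 1% for Wald and 7% to 9% for likelihood ratio.
- Two centres with no effect and two with an SE rate of 5%: power 2% to 9% by Wald, 51% to 68% by likelihood ratio.
- In a separate set of heterogeneity scenarios the Firth-penalised likelihood-ratio test had size 2.5% to 2.9% and power 22% to 64%, against 1% to 18% for Wald and 46% to 80% for the ordinary likelihood ratio.

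**The case against.** The article says logistic regression and no more. Firth-penalised and exact logistic regression are logistic regression too, and the choice of test or a sparse-cell fallback is normally settled in an analysis plan that is not shown. Showing results stratified by centre may already mean counts per arm. An observed odds ratio of 0 describes an empty cell correctly, and an analyst would notice it. The trial is exploratory, no decision is tied to this analysis, centre sizes are assumed, and at an SE rate of 20% with equal centres the risk falls to 23% to 34%.

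Much of this stands, and it limits the weight of the point. It does not remove it. The article does fix a method for centre, the same one as for phase, and it does so after judging events too few for centre in the primary model. Equal centres give the lowest risk, so uncertainty about centre size makes the problem larger.

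A reader might infer that the heterogeneity test almost cannot reject, so that it would report no heterogeneity whatever the data show. The documents do not support that. It is true of a Wald test only, and no test is named. An ordinary likelihood-ratio statistic stays finite with empty cells and errs the other way, rejecting too often. A reader might also infer that the phase model is free of the problem. Its 3% to 6% assumes equal halves, which the enrolment to date makes doubtful.

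**Conclusion.** The point holds as a minor improvement. At the plan's own rates and size, 43% to 56% of trials with equal centres would have at least one degenerate arm-by-centre cell, and 52% to 72% under the assumed unequal splits. In those trials a centre odds ratio is 0 or infinite with no finite Wald interval. Neither usual maximum-likelihood test holds its 5% level: Wald is nearly powerless (size below 1%) and the ordinary likelihood ratio is anti-conservative (about 7% to 9%). The figures rest on 45% and 15% being right and on assumed centre sizes. The phase model is much less affected. The primary analysis omits centre and is untouched.

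**What to change.** For centre, replace the reference to the phase approach by two steps, both labelled exploratory. First, tabulate T2EL counts per arm and centre with the risk difference and its Newcombe 95% interval, which can be computed when a cell is empty. Second, run one prespecified heterogeneity test, by Firth-penalised likelihood ratio or Zelen's exact test, and report no Wald or ordinary maximum-likelihood test from the interaction model.

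The cost is analysis-plan wording and standard software; data collection and recruitment do not change. The drawback is that the penalised test is somewhat conservative (size about 2.5% to 3%) and has less power than the ordinary likelihood-ratio test, whose extra power comes with an inflated error rate. Any centre comparison of this size remains weak, so a non-significant result should not be read as evidence of consistency.
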